## Abstract

**Background:**

Atopic dermatitis (AD) is associated with reduced skin microbial diversity and overgrowth of *Staphylococcus (S.) aureus*. However, the importance of *S. aureus* colonisation in the complex pathogenesis remains unclear and studies on the effect of anti-staphylococcal therapy in non-infected AD show contradictory results. Long-term interventions against *S. aureus* might be needed to restore the microbial balance, but carry the risk of bacterial resistance induction. Staphefekt, an engineered bacteriophage endolysin, specifically kills *S. aureus* leaving other skin commensals unharmed. Bacterial resistance towards endolysins has not been reported, nor is it expected, which allows us to study its effect as long-term anti-staphylococcal treatment in non-infected AD.

**Methods:**

This is a multi-centre, placebo-controlled, double-blinded and randomized superiority trial with a parallel group design. A total of 100 participants, aged 18 years or older, diagnosed with moderate to severe AD and using a topical corticosteroid in the weeks before enrolment are included in the study. The study is executed in the Erasmus MC University Medical Centre Rotterdam in collaboration with the Havenziekenhuis Rotterdam. After a 2-week run-in period to standardize the corticosteroid use with triamcinolone acetonide 0.1% cream, participants will be randomized to either treatment with Staphefekt in a cetomacrogol-based cream or a placebo for 12 weeks, followed by an 8-week follow-up period. The primary objective is to assess the difference in the need for corticosteroid co-therapy between the Staphefekt and the placebo group, measuring the number of days per week of corticosteroid cream (triamcinolone) use. Secondary outcomes include the difference in use of corticosteroid cream measured in grams, differences in clinical efficacy, quality of life (QoL), microbial composition (includi23ng *S. aureus*) between the Staphefekt and the placebo group, and the safety and tolerability.

**Discussion:**

The results of this trial will provide data about the effect of long-term anti-staphylococcal therapy with Staphefekt on corticosteroid use, clinical symptoms and QoL in patients with moderate to severe AD. Additional data about growth characteristics of the skin microbiome, including *S. aureus*, will give insight into the role of the microbiome as a factor in the pathophysiology of AD.

**Trial registration:**

ClinicalTrials.gov, NCT02840955. Registered on 11 July 2016.

**Electronic supplementary material:**

The online version of this article (doi:10.1186/s13063-017-2118-x) contains supplementary material, which is available to authorized users.

## Background

Atopic dermatitis (AD) is a chronic inflammatory skin disease that is associated with reduced quality of life (QoL), primarily due to itchy skin [1–3]. The disease is characterised by reduced skin microbial diversity and overgrowth of *Staphylococcus (S.) aureus,* a bacterium that can aggravate skin inflammation via the production of staphylococcal enterotoxins that stimulate the release of pro-inflammatory cytokines [4–7]. However, the importance of *S. aureus* colonisation in the complex pathogenesis, compared to the other genetic and immunologic factors involved, remains unclear.

Current treatment approaches for AD include topical treatment with emollients and anti-inflammatory therapy with (topical) immunosuppressive agents (corticosteroids and calcineurin inhibitors), according to the international guidelines [8, 9]. Anti-staphylococcal therapy is only recommended in cases of fever or clinically infected skin [8, 9]. Clinical studies that evaluated the added value of anti-staphylococcal therapy in non-infected AD, have shown contradictory results. Bath Hextall et al. performed a systematic review of 26 studies and showed that anti-staphylococcal agents reduced the amount of *S. aureus* on the skin in AD. However, the bacteriological reduction did not translate into a decrease in clinical symptoms [10]. These studies mainly investigated short-term therapies of less than one month duration and comprised small and poor-quality studies. As discontinuation of therapy after a short treatment period can result in quick regrowth of *S.* aureus [11], the results of this systematic review do not necessarily mean that anti-staphylococcal agents do not work. A more recent review by Brüssow et al. summarizes two intervention trials that reported significant reduction in disease severity in non-infected AD after 2 and 3 months of therapy with anti-staphylococcal therapy (bleach baths) [12–14]. We hypothesize that long-term therapy may be needed to reduce *S. aureus* overgrowth and maintain a stable and balanced skin microbial composition. Ultimately, this could result in disease improvement, prevention of AD flares and less need for (topical) immune suppression. However, long-term use of antibiotics can induce bacterial resistance [15], and both the use of antibiotics and dilute bleach baths can cause unnecessary harm to the commensal flora, that is hypothesized to have anti-staphylococcal properties [16].

In the context of the increasing incidence of bacterial resistance, the interest in bacteriophages and their endolysins as antibacterial therapy has been renewed [17]. Staphefekt SA.100 is an engineered chimeric endolysin that specifically lyses the cell membrane of *S. aureus* via endopeptidase and putative amidase activities [18–20]. Long-term application of Staphefekt on the skin, targeting only *S. aureus* and leaving skin commensals unharmed, may improve long-term AD outcomes, such as the number of disease flares, and may reduce the use of topical corticosteroids. Bacterial resistance to Staphefekt or other endolysins has not been observed and could not be induced, which enables us to study the effect of long-term anti-staphylococcal treatment in non-infected AD using this endolysin-based agent [19, 21, 22].

The aim of this randomized controlled trial, the MAAS trial, is to evaluate the effect of 3-month anti-staphylococcal therapy with Staphefekt on the frequency and quantity of topical corticosteroid use, clinical symptoms and QoL in patients with moderate to severe AD. In addition, data on the growth characteristics of the skin microbiome, including *S. aureus*, will be collected, which will gain insight into the role of the microbiome as a factor in the pathophysiology of AD.

## Methods/design

### Design and setting

The MAAS trial (Microbiome in atopic dermatitis during anti-staphylococcal therapy and the effect on steroid use), is a multi-centre, randomized, double-blinded, placebo-controlled superiority trial with a parallel group design (Fig. 1). The study aims to evaluate the effect of Staphefekt on the use of corticosteroids, disease severity, QoL and composition of the microbiome in patients with AD. The study was designed by the Department of Dermatology of the Erasmus MC University Medical Centre Rotterdam and will be executed in collaboration with the Havenziekenhuis Rotterdam. Enrolment and follow-up visits take place at these two locations. Participants who comply with the criteria for inclusion and exclusion will start with a 2-week run-in period to standardize the corticosteroid use with triamcinolone acetonide 0.1% cream. After completion of the run-in phase, participants will be randomized to either treatment with Staphefekt or a placebo for 12 weeks, followed by an 8-week follow-up period. An Eczema Area Severity Index (EASI) above 50 after the run-in phase is a contraindication for further participation. During the course of the study, participants visit the outpatient clinic six times (visit 1 through 6) and data will be collected on corticosteroid use, disease severity, QoL, skin microbiome and adverse events. See Additional file 1 for an overview of the Standard Protocol Items: Recommendations for Interventional Trials (SPIRIT) 2013 checklist items. See Table 2 for the SPIRIT diagram of the trial procedures.

**Fig. 1 Fig1:**
[figure not shown]
Flowchart of the study design

### Ethical considerations

This study follows the Dutch Medical Research Involving Human Subjects Act 1998 (WMO) and the principles of the Helsinki Declaration 2008. All study procedures have been reviewed and approved by the Medical Ethics Committee of the Erasmus MC University Medical Centre Rotterdam, The Netherlands (reference 2016-233). Protocol amendments will be submitted for review at the Medical Ethics Committee.

### Participants

This study will enrol adults (18 years or older) diagnosed with AD according to the UK working party diagnostic criteria for AD [23–25]. Participants are eligible for enrolment if they have a score between 7.1 and 50.0 on the EASI for disease severity. Topical corticosteroids must have been prescribed before enrolment. All patients must be able to read and understand the patient information and provide written informed consent. Patients are not eligible for enrolment if they used: (1) systemic antibiotics or corticosteroids in the 2 months prior to enrolment, (2) oral immunosuppressive agents or UV therapy in the 3 months before enrolment or (3) local antibiotics or Staphefekt (from commercial sources) 1 week before enrolment. Other criteria for exclusion are known contact allergy to any of the components of the study drug (e.g. propylene glycol), clinically infected AD or the existence of other skin condition(s) that could interfere with the assessment of the AD severity.

### Recruitment, inclusion and consent

Participants with AD will be recruited from the dermatology outpatient clinic of the Erasmus MC and the Havenziekenhuis Rotterdam. Furthermore, Dutch dermatologists are informed about the study via the Dutch Trial Network and via scientific conferences. Patients with AD are informed via the patient support group and via online media, such as DermHome (https://www.huidhuis.nl/). In addition, recruiting advertisements will be placed on student forums and in local newspapers. Patients who are interested in participation in the trial can contact the researcher directly via email or phone. After a first screening with regard to the inclusion and exclusion criteria via email or phone, potentially eligible participants receive an information letter and will be invited to the dermatology outpatient clinic to further assess eligibility. Patients who fulfil the inclusion criteria and are willing to participate, will be included in the study after providing written informed consent.

### Sample size

The sample size for this study was calculated based on the primary outcome, namely the difference in mean days per week of corticosteroid use over 12 weeks between the Staphefekt arm and the placebo arm, in patients who are positive for *S. aureus* on the skin at baseline. This is the first study measuring clinical outcomes of Staphefekt in patients with AD. We expect to find a mean topical corticosteroid use of 5 days/week in the placebo group. This was based on a study by Hon et al. that showed decreased use of topical corticosteroids when taking bleach baths, an anti-staphylococcal therapy [26]. Based on the results of this study, we anticipate an effect size of 1.25 day/week reduction in topical corticosteroid use in the Staphefekt arm. A sample size was calculated using the unpaired *t* test to compare means in a superiority trial design. With power of 0.80, alpha of 0.05 and SD of 2.0, 40 patients are needed per treatment arm. Assuming 10% drop out and 90% of the patients being positive for *S. aureus* on the skin lesions, 50 patients will be assigned to each of the two treatment arms.

### Randomization and blinding

The participants are randomly assigned, in a 1:1 fashion to either treatment with Staphefekt or placebo. Stratified block randomization for AD severity is performed to ensure equal distribution of patients with moderate and severe AD over the treatment arms (EASI 7.1–21 and EASI 21.1–50). Randomization is done by an independent biostatistician of the Erasmus MC, using the statistical software package R version 3.2.2. The participants, the researchers and laboratory analyst are blinded to the intervention. The pharmacy manages the randomization list and provides blinded study medication.

### Intervention

After enrolment, all participants start a run-in phase of 2 weeks in which they receive a standardized dosing regimen of topically applied triamcinolone acetonide 0.1% cream (Table 1). After the run-in period, the patient and the researcher evaluate further participation, with very severe AD (EASI >50) as a contraindication for continuation. The run-in period and randomization is followed by a 12-week treatment period and an 8-week follow-up period. During the treatment period, Staphefekt or placebo cream will be applied on the total skin surface twice daily to reach optimal reduction of *S. aureus,* as both lesional and non-lesional skin are often colonised [4]. The Staphefekt endolysin is made available in a cetomacrogol-based cream. The placebo is composed of the same cetomacrogol-based cream, without Staphefekt. During the treatment and follow-up period triamcinolone will be used according to the corticosteroid dosing regimen (Table 1). Measurements and assessments will be performed at enrolment (start of the run-in phase, visit 1), baseline (start treatment with Staphefekt/placebo, visit 2a), 0.5 hours after baseline and 2, 6, 12 and 20 weeks after baseline (visit 2b to 6). Table 2 provides an overview of the measurements per visit. Unless it is in the best interest of the patients (for example in the case of an eczema flare), patients are not allowed to use systemic or topical immunosuppressive medication (including calcineurin inhibitors), antibiotics or antiseptics during the study. Escape medication will be prescribed according to current treatment guidelines and its use will be registered. At the start of the study, patients receive an emollient according to the patient’s preference for use during the course of the study. The use of this emollient will be registered by weighing the tubes at each visit.

**Table 1 Tab1:** Corticosteroid dosing regimen

	Week 1	Week 2	Week 3	Week 4	Week 5	Week 6	Week 7	Week 8	Week 9
Saturday	X X	X	X	X					
Sunday	X X	X			X	X	X	X	
Monday	X X	X	X	X					
Tuesday	X X	X			X	X			
Wednesday	X X	X	X	X					
Thursday	X X	X			X	X	X	X	
Friday	X X	X	X	X					

Start in week 1 or 2 depending on severity of the atopic dermatitis. If the symptoms allow, reduce the use of corticosteroid cream weekly according to the scheme. Return to week 1 or 2 in the case of an exacerbation. Based on patient assessment

**Table 2 Tab2:**
[figure not shown]
SPIRIT diagram of study procedures [28–32]

Visit 1, enrolment in the trial and start of a 2-week run-in phase; visit 2a, start of the intervention (baseline); visit 2b, 0.5 hours after baseline; visit 3, 2 weeks after baseline; visit 4, 6 weeks after baseline; visit 5, 12 weeks after baseline and end of the intervention; visit 6, follow-up visit 20 weeks after baseline. All visits take place plus or minus 2 days from the indicated timeframe. *EASI* Eczema Area and Severity Index, *IGA* Investigator’s Global Assessment, *Pruritus NRS* Pruritus Numerical Rating Scale, *POEM* Patient Orientated Eczema Measure

### Detailed sample and laboratory procedures

Sampling procedures are based on the “Manual of Procedures” for microbiome sampling of the Human Microbiome Project [27]. All samples are obtained by one of the researchers wearing gloves (sterile for the skin scrub). Sterile Copan 490CE.A swabs are used to sample the skin, nasal cavity and pharynx. Skin samples are taken from lesional skin, preferably located at the antecubital folds or the popliteal fold. The skin surface is swabbed for 30 seconds. The mucosal surfaces of both the anterior nares are gently rubbed, going round the area for 10 seconds. The rear of the oropharynx is swabbed for 5 seconds using a tongue depressor. For the skin scrub sample, a ring with an internal diameter of 4 cm will be placed on the same skin lesion where the swab was collected, but on a non-overlapping area: 1 ml of swab solution (0,85% NaCl, 0.1% bacteriological peptone, 0.1% Tween 80) is pipetted into the ring. After rubbing over the skin with a Copan 480CE swab for 1 minute, the swab solution will be pipetted out of the ring into an Eppendorf tube. The swabs will be sent to the laboratory by mail on the day of collection. A semi-quantitative culture technique and matrix-assisted laser desorption ionization time-of-flight (MALDI-TOFF) for identification of *S. aureus* will be performed. The scrub samples will be stored at –80 °C at the Erasmus MC Rotterdam until 16S rRNA-sequencing and quantitative *S. aureus* analysis.

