### Primary and secondary outcomes

The primary outcome of this study is the days per week of corticosteroid use, compared between the Staphefekt and the placebo group over 12 weeks. Patients report their triamcinolone use daily in a secured digital platform, “DermHome”.^1^ Additionally, the use of triamcinolone cream will be measured in grams by weighing the study medication at the time of issue and return (each visit). Secondary outcomes include clinical efficacy and QoL from baseline through week 12 and week 20, change in the microbial composition (including *S. aureus)* and safety. Clinical efficacy is measured using the EASI, the Investigator’s Global Assessment (IGA) and registration of the number of flares [28]. A flare is defined as an exacerbation that requires the need to intensify treatment, from a doctor or patient’s perspective. This implies stronger topical therapy or the need for systemic treatment. A 50% increase in the EASI score compared to baseline is used as an indication to intensify treatment. The Pruritus Numerical Rating Scale (Pruritus NRS) and the Patient Orientated Eczema Measure (POEM) are included as patient-reported efficacy outcomes [29, 30]. QoL is measured using the Skindex-29 [31, 32]. Changes in the microbiome are evaluated by comparing the changes in bacterial composition between the treatment groups, determined by 16S rRNA sequencing of the skin scrub samples. Reduction in *S. aureus* is determined by quantitative PCR (and culture for the comparison between visit 2a and visit 2b). Safety and tolerability is assessed by monitoring the incidence of (serious) adverse device events through the end of the study, evaluated by medical check-ups that include evaluation of vital signs. Reportable adverse events will be reported within the set timelines to the competent authorities. Table 2 gives a detailed overview of the measurements per visit.^1^

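### Skin samples follow the lesion, not the baseline site, so the S. aureus and microbiome changes at weeks 2 to 20 may be biased if lesions clear more in one arm

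*Protocol article*

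**What the plan says.** The section Detailed sample and laboratory procedures of the protocol article chooses the skin site by its disease state and treats location as a preference: "Skin samples are taken from lesional skin, preferably located at the antecubital folds or the popliteal fold". The one reference to an identical lesion concerns the scrub, which is "placed on the same skin lesion where the swab was collected, but on a non-overlapping area". That links two samples taken at the same visit; it does not link one visit to another.

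The section Primary and secondary outcomes defines the microbiological endpoints as change. The microbiome endpoint rests on "comparing the changes in bacterial composition between the treatment groups, determined by 16S rRNA sequencing of the skin scrub samples". For the other endpoint, the article states that a fall in the staphylococcal load "is determined by quantitative PCR (and culture for the comparison between visit 2a and visit 2b").

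The section Intervention places the assessments after the start of treatment at "0.5 hours after baseline and 2, 6, 12 and 20 weeks after baseline (visit 2b to 6"). The table that would show which samples are taken at which visit is a figure and is not available here.

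**The concern.** After randomisation, whether a fold is still lesional is itself a result. The trial measures it through EASI and IGA as efficacy outcomes. A site rule that depends on lesion status therefore selects the follow-up sample on an outcome, while the endpoint is labelled as change from baseline.

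If the baseline lesion has cleared, a literal reading leaves two possibilities. The sample is taken from a lesion that persists elsewhere, so that change compares two different sites. Or no lesion is left, so that there is no eligible site and the sample is missing because the patient did well.

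The S. aureus and microbiome results are the trial's evidence on mechanism. If Staphefekt clears more lesions than placebo, the skin where it worked best would be the skin least likely to be sampled.

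**Working it through.** **1. What the text fixes.** The site rule names lesional skin and prefers the elbow or knee folds. It makes no distinction between baseline and follow-up. No sentence covers a lesion that has cleared or a patient without lesions. The endpoints, by contrast, are changes compared between arms. The two sections do not contradict each other in words, but the rule does not secure that a change is measured at one site.

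**2. Which comparisons are exposed.**
- Visit 2a against visit 2b: 0.5 hours apart, so clearing cannot matter.
- The cultures at visits 1 and 2a that define S. aureus-positive and negative patients: taken before treatment starts, so not affected.
- The primary outcome: days of triamcinolone use reported daily by the patient, so not affected.
- PCR and 16S changes at weeks 2, 6, 12 and 20, wherever skin is sampled at those visits: exposed.

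**3. Size.** The article gives no variance, effect size or clearance rate for the microbiological endpoints, so there is no figure to reproduce. Its sample size concerns the primary outcome only. What follows is an illustration on assumed values.

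Let p_A and p_P be the proportions with a cleared baseline site in the Staphefekt and placebo arms, d the log10 gap in load between persisting and cleared skin, and e a direct effect of Staphefekt on all skin.

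- Fixed baseline site: mean change is −e − p_A·d on Staphefekt and −p_P·d on placebo. The contrast is −e − (p_A − p_P)·d.
- Sample moved to a persisting lesion: mean change is −e and 0. The contrast is −e.
- Part of the contrast lost by moving: (p_A − p_P)·d.

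This assumes that the new lesion started at the same load as the baseline lesion, that d is the same in both arms, and that e is the same on all skin. Under these assumptions e cancels. With e = 0.5, 50% against 30% and d = 1.0, the fixed-site contrast is −0.5 − 0.2 = −0.70, the moved contrast is −0.50, and the loss is 0.20.

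With placebo clearance assumed at 30%, the loss in log10 is:

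| Clearance on Staphefekt | d = 0.5 | d = 1.0 | d = 1.5 |
|---|---|---|---|
| 30% | 0 | 0 | 0 |
| 40% | 0.05 | 0.10 | 0.15 |
| 50% | 0.10 | 0.20 | 0.30 |
| 60% | 0.15 | 0.30 | 0.45 |

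The sign follows p_A − p_P. The loss is toward no difference when Staphefekt clears more, and zero when clearance is equal.

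**4. Precision under equal clearance.** At a fixed site the site's own level cancels from the change. If the sample moves between independent sites with within-patient site variance σ², the change for that patient gains 2σ² of variance. The article gives no value for σ².

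**5. Missing samples.** The article relies on the mixed model to cope with missing data. That holds when the missingness is explained by data in the model. A sample absent because the skin has cleared meets this condition only if clearance, or a good proxy for it, is in the model.

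**The case against.** **The article is a condensation.** It says its sampling follows an external manual, and the visit table is not shown. The full protocol or sampling manual may fix the site and handle cleared lesions. This stands as a limit: the article does not show that the trial sampled wrongly. But the point is not mere silence. The article states a rule, in a section detailed enough to give swabbing times and ring diameter, and that rule followed as written gives the problem.

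**Load on current lesions is a legitimate target.** Sampling active lesions asks whether the product lowers S. aureus on diseased skin. A fixed site mixes bacterial killing with healing, and healing also depends on triamcinolone, which follows symptoms in both arms: "If the symptoms allow, reduce the use of corticosteroid cream weekly according to the scheme". The mixing is a real cost of the fixed site. Yet the article nowhere declares current lesions as the target, and samples from them would still be selected by disease state after randomisation.

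**The numbers are assumed.** The cream goes on everywhere, "cream will be applied on the total skin surface twice daily", so persisting lesions in the Staphefekt arm are treated too and need not keep their baseline load. The algebra above allows for this with a uniform direct effect, which cancels, but no clearance rate or load gap comes from the article. Symptom-guided steroid use may also bring clearance in the two arms closer together, so zero belongs in the range.

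A reader might infer that the sample certainly moves in responders, that the contrast is biased by a definite log10 amount, or that every S. aureus result in the trial is affected. The article supports none of these. The move is inferred from the rule, the bias needs clearance to differ between arms, and the comparisons that precede or immediately follow the first application are safe.

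**Conclusion.** The point holds in conditional form. The published rule lets the sampling site depend on disease state after randomisation and has no provision for a cleared lesion, while the endpoints are changes compared between arms. The contrasts at weeks 2 to 20 may therefore be biased, probably toward no difference if Staphefekt clears more lesions. With equal clearance, and the same load gap in both arms, there is no bias in the contrast by this route, only added variation. The size cannot be computed from the article; 0 to 0.45 log10 is what the assumed ranges give and nothing more.

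The consequence is limited to secondary, mechanistic endpoints in a study that describes itself as hypothesis generating. It is worth correcting because the correction is cheap and these endpoints are meant to explain the clinical result.

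**What to change.** Add to the sampling procedure: at visit 2a, name one index site per patient that is lesional at that visit, and record the fold and side. Take the swab and the scrub from that site at every later visit, whatever its state. Record at each sampling whether the site is lesional, and use that record descriptively. If a sample from a current lesion is also wanted, label it as such and report it separately.

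The cost is a short addition to the procedure and a field on the case report form; the index-site rule needs no extra samples. The downside is that some late samples will come from healed skin, so the contrast includes the effect of healing as well as direct bacterial killing. The report should say so. If the full protocol or manual already fixes the site, stating that rule in the article is enough.
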